## 5. Study Medications

### 5.1 Basic Information of Medications

- **Dexamethasone Sodium Phosphate Injection**
  - Manufacturer: Chendxin Pharmaceutical Co., Ltd.
  - Dosage form: Injection
  - Route of administration: Intravenous injection
  - Specification: 1 ml: 5 mg
  - Storage and stability: Protect from light, keep tightly closed, store at or below 25°C (do not freeze), shelf life of 24 months.
- **Netupitant and Palonosetron Hydrochloride Capsules**
  - Trade name: Akynzeo
  - Manufacturer: Helsinn Birex Pharmaceuticals Ltd.
  - Dosage form: Hard capsules
  - Route of administration: Oral

- Specification: Each hard capsule contains 0.3 g of netupitant (0.1 g per tablet × 3 tablets) and 0.5 mg of palonosetron hydrochloride (calculated as C19H24H2O, 1 soft capsule).
- Storage and stability: Store at room temperature (below 30°C), sealed, shelf life of 36 months.

## 5.2 Dosing Regimen

### 5.2.1 Drug Dose

- **Control Group:** 8 mg of dexamethasone is given intravenously 0.5 hours before chemotherapy, and 1 capsule of netupitant and palonosetron hydrochloride capsules (each capsule contains 0.3 g of netupitant and 0.5 mg of palonosetron hydrochloride) is taken orally 1 hour before chemotherapy.
- **Experimental Group:** 5 mg of dexamethasone is given intravenously 0.5 hours before chemotherapy, and 1 capsule of netupitant and palonosetron hydrochloride capsules (each capsule contains 0.3 g of netupitant and 0.5 mg of palonosetron hydrochloride) is taken orally 1 hour before chemotherapy.

### 5.2.2 Drug Discontinuation Criteria During Treatment

Drug discontinuation is recommended when patients experience severe adverse events or specific types of adverse events, such as severe drug intolerance or allergic reactions.

## 5.3 Concomitant Medication

Concomitant medication/treatment is given at the discretion of the investigator based on the interests of the subjects. All treatments and medications (excluding solvent medications) used within 28 days before signing the informed consent form until the end of the safety follow-up period should be strictly recorded in the eCRF in accordance with GCP regulations. If the subjects experience adverse events (AE), they should be closely observed and actively treated symptomatically if necessary. The medical documents should be fully recorded and the drugs and non-drug treatments used should

be recorded and explained in the eCRF. After the above collection period, only concomitant medications and non-drug treatments related to the study drug for AE/SAE should be recorded.

### **5.3.1 Permitted Medications Prior to Study**

Participants who have received corticosteroids or any other antiemetic medications before screening but have discontinued them for at least 7 days at the time of screening.

### **5.3.2 Permitted Medications During the Study**

Metoclopramide is uniformly used as the first-choice rescue medication during the study. Refractory CINV is managed in accordance with guidelines and the attending physician's opinion.

### **5.3.3 Prohibited or Cautiously Used Medications and Treatments During the Study**

During the study, the use of any other antiemetic medications other than metoclopramide (unless deemed necessary by the investigator) is prohibited.

## **5.4 Medication Adherence**

Medication adherence in this study is the responsibility of the principal investigator. Patients who do not meet the criteria for analysis will not be included in the final analysis.

## **6 Study Procedures**

This study is divided into three phases: screening phase, treatment phase, and follow-up phase.

## 6.1 Screening Phase

The screening phase begins with the signing of the informed consent form (ICF) by participants who meet the criteria of this study and ends with enrollment or screening failure. Participants who discontinue the study after signing the informed consent form but before enrollment will be considered as "screening failures."

The following screening steps must be completed within 14 days before starting the study drug treatment:

- Obtain written informed consent signed by the participant;

- Collect demographic information;

- Collect medical and treatment history;

- Collect medication history;

- Conduct physical examination and ECOG PS score;

- Laboratory tests, such as screening for infectious diseases, routine urinalysis, and stool examination;

- Collect relevant imaging results for tumor baseline assessment, such as chest and abdominal CT, brain MRI, bone ECT, etc.;

- Evaluate concomitant medications and treatments currently in use.

The following screening steps must be completed on the day of starting the study drug treatment:

- Physical examination, vital signs, and ECOG PS score;

- Laboratory tests, such as complete blood count, biochemical profile, coagulation function, etc.

## 6.2 Treatment Phase

The treatment phase begins with the administration of the study drug and continues until the completion of this round of cancer treatment, disease progression, death, loss to follow-up, or initiation of new anti-cancer treatment, whichever occurs first. Participants should start receiving the study drug within 24 hours of enrollment.

## **6.3 Follow-up Phase**

### **6.3.1 End of Study Treatment/Withdrawal Visit**

Participants should complete the end of study treatment/withdrawal visit when they discontinue the study. If participants do not have relevant test results within 7 days before the end of treatment, the tests specified in the protocol should be conducted within 7 days after the end of treatment. The following items should be completed at the end of treatment/withdrawal: [Complete Blood Count] [Biochemical Profile] [Vital Signs] [Physical Examination] [ECOG Score] [Adverse Events] [Concomitant Medications/Treatments].

### **6.3.2 Safety Follow-up Visit**

Seven days ( $\pm 3$  days) after the last administration of the study drug, regardless of whether the participant has started new anti-cancer treatment, the participant should return to the research center for a safety follow-up visit and complete the following safety assessment indicators. If a participant is unable to resume study drug administration due to an AE, the last administration date is determined as the last dose date. If this date is more than 7 days ( $+3$  days) from the time they were judged to need to discontinue study treatment, this situation does not need to be recorded as a protocol deviation, but it is recommended that the participant return to the research center for a safety follow-up visit as soon as possible. The following items should be completed at the 7-day visit after the last administration of the study drug: [Complete Blood Count] [Biochemical Profile] [Vital Signs] [Physical Examination] [ECOG Score] [Adverse Events] [Concomitant Medications/Treatments].

## **7 Efficacy Evaluation**

### **7.1 Primary Efficacy Endpoint**

Complete response rate (no vomiting and no use of rescue medication within 7

days after administration of the study drug).

## 7.2 Secondary Efficacy Endpoints

CRR during acute (0-24h), delayed (24-120h), and long-delayed (120-168h) phases.

## 7.3 Exploratory Efficacy Endpoints

TCR and CCR during acute, delayed, long-delayed, and overall post-chemotherapy phases.

CINV incidence patterns and daily occurrence rates across each period.

# 8 Safety Evaluation

Safety evaluation includes the recording of adverse events (AEs) and serious adverse events (SAEs) from the time participants sign the informed consent form until the end of the study, through vital signs, physical examination, laboratory tests, electrocardiogram, echocardiogram, abdominal ultrasound, etc. The safety of the study drug is evaluated according to the Common Terminology Criteria for Adverse Events (CTCAE) version 5.0, and the incidence and severity of nausea and vomiting events are recorded in accordance with the NCCN (2024.V1) Clinical Practice Guidelines. Participants should be closely monitored for changes in symptoms and signs after drug administration during the study. Any AEs that occur should be promptly managed to ensure the safety and well-being of the participants. After timely management of AEs, their diagnosis (or symptoms if no diagnosis is made), onset and resolution dates, severity, relationship to the study drug, whether treatment was required, management measures, and outcomes should be recorded, followed by analysis, evaluation, and statistical analysis of the AEs.

All participants must undergo comprehensive physical and laboratory examinations during the study, including measurement of temperature, pulse, respiration, blood pressure, complete blood count, urine routine, biochemical profile,

coagulation function, 12-lead electrocardiogram, echocardiogram, and abdominal ultrasound. If clinically significant abnormal changes occur, they should be closely monitored and managed until they return to normal or baseline levels or stabilize.

## **8.1 Physical Examination and Vital Signs**

Physical examination is conducted by the study physician and includes the following: general condition, skin and mucous membranes, lymph nodes, head, eyes, ears, nose, throat, neck, chest, abdomen, musculoskeletal system, neurological reflexes, respiratory system, cardiovascular system, genitourinary system, and mental status. Weight should be measured each time a physical examination is conducted, while height needs to be measured only once during the screening period.

Vital signs include the following: temperature, blood pressure, respiratory rate, and heart rate.

The ECOG score is assessed by the study physician according to the "Performance Status Score (ECOG)" in Appendix I.

## **8.2 Laboratory Tests**

Laboratory test samples will be collected at the time points specified in the "Clinical Trial Flowchart."

Complete blood count: A complete blood count is repeated twice after each chemotherapy cycle, and the frequency of testing can be increased if there are abnormal laboratory results.

Biochemistry: Biochemical tests are repeated once a week, and the frequency of testing can be increased if there are abnormal laboratory results.

## **8.3 Nausea and Vomiting Assessment**

Investigators will record the incidence and severity of nausea and vomiting events according to the NCCN (2024.V1) and CTCAE (V5.0) Clinical Practice Guidelines.

## **8.4 Adverse Events (AEs)**

### **8.4.1 Definition of Adverse Events**

An adverse event is any untoward medical occurrence in a participant in a clinical trial after signing the informed consent form, but it does not necessarily have a causal relationship with the study drug. An adverse event can be any unexpected, unfavorable symptom, sign, disease, or abnormal laboratory finding, regardless of whether it is related to the study drug. Adverse events include the following situations: 1) pre-existing medical conditions/diseases before the start of study treatment, which are only considered adverse events if they worsen after the initiation of the study drug; 2) any new adverse events; 3) abnormal laboratory values or findings, which are considered adverse events only if they are deemed clinically significant.

### **8.4.2 Criteria for Assessing the Severity of Adverse Events**

Refer to the grading criteria for drug adverse events in CTCAE version 5.0. If an adverse event not listed in the CTCAE version 5.0 tables occurs, the following criteria may be used:

- Grade I: Mild; no clinical symptoms or only slight clinical symptoms; detected only clinically or diagnostically; no treatment required.
- Grade II: Moderate; requiring minimal, topical, or non-invasive treatment; limitation of instrumental activities of daily living (ADL), which include cooking, shopping, making phone calls, managing finances, etc.
- Grade III: Severe or medically important but not immediately life-threatening; resulting in hospitalization or prolonged hospital stay; causing disability; limitation of self-care ADL, which include bathing, dressing, undressing, eating, toileting, taking medications, etc., but not bedridden.
- Grade IV: Life-threatening consequences; requiring urgent treatment.
- Grade V: Death related to the adverse event.

### **8.4.3 Criteria for Assessing the Relationship Between Adverse Events and the Study Drug**

All adverse events, including any unexpected clinical manifestations that occur after signing the informed consent form, regardless of whether they are related to the study drug or even whether the drug was administered, should be reported as adverse events. All adverse events must be reported in the form of a clinical report. Any discomfort reported by the patient during the treatment period or any abnormal changes in objective laboratory test indicators should be accurately recorded, along with the severity, duration, management measures, and outcomes of the adverse events. Investigators should also comprehensively assess the relationship between adverse events and the study drug, using a five-category classification method to evaluate the potential association between adverse events and the study medication: "definitely related," "probably related," "probably not related," "definitely not related," and "unable to determine." "Definitely related," "probably related," and "unable to determine" are all classified as drug adverse reactions. When calculating the incidence of adverse events, the sum of these two categories is used as the numerator, and the total number of participants used for safety evaluation is used as the denominator. The criteria for judgment are as follows:

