**Notes:**

- \*Safety follow-up will be conducted within 7 days after the last administration of netupitant/palonosetron capsules.
- a. Vital Signs: Including body temperature, blood pressure, pulse, and respiratory rate. Blood pressure should be measured as systolic and diastolic pressures after resting in a seated position for 5 minutes, and measurements should be taken at the same time and with the same sphygmomanometer whenever possible.
- b. Complete Blood Count: White blood cell count (WBC), neutrophil count (NEUT), neutrophil percentage, lymphocyte count (LYMPH), lymphocyte percentage, monocyte count, monocyte percentage, eosinophil count, eosinophil percentage, basophil count, basophil percentage, red blood cell count (RBC), hematocrit (HCT), mean corpuscular volume (MCV), mean corpuscular hemoglobin (MCH), mean corpuscular hemoglobin concentration (MCHC), hemoglobin (Hb), platelets (PLT).

- c. Urinalysis: Protein (PRO), glucose (GLU-U), microscopic WBC, microscopic RBC, casts, occult blood.
- d. Biochemical Profile: Aspartate aminotransferase (AST), alanine aminotransferase (ALT), gamma-glutamyl transferase (GGT), lactate dehydrogenase (LDH), total bilirubin (TBIL), direct bilirubin (DBIL), total protein (TP), albumin (ALB), alkaline phosphatase (ALP), triglycerides (TG), total cholesterol (TC), sodium (Na+), potassium (K+), chloride (Cl), total calcium (Ca2+), glucose (GLU), urea (Urea) and/or blood urea nitrogen (BUN), creatinine (Cr), uric acid (UA).
- e. Coagulation Function: Prothrombin time (PT), activated partial thromboplastin time (APTT), thrombin time (TT), fibrinogen (FIB), international normalized ratio (INR), D-dimer (DD).
- f. Pregnancy Test: Only for women of childbearing potential. Blood pregnancy test will be conducted at the screening visit, and urine pregnancy test may be performed at other visits as deemed appropriate by the investigator.
- g. Thyroid Function: Free triiodothyronine (FT3), free thyroxine (FT4), thyroid-stimulating hormone (TSH).
- h. Viral Serology: Including hepatitis B surface antigen, hepatitis B surface antibody, hepatitis B e antigen, hepatitis B e antibody, hepatitis B core antibody, hepatitis C antibody, HIV antibody, syphilis antibody.
- i. Participants should ensure medication adherence as required by the protocol. If a dose is missed, the participant should continue taking the prescribed amount on the next day without doubling the dose.

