### **2.2.3 Secondary Safety Endpoints**

Treatment related adverse events (evaluated using the National Cancer Institute Common Terminology Criteria for Adverse Events (NCI CTCAE) version 5.0).

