**Table 2: Criteria for Assessing the Relationship Between AEs and the Investigational Drug**

| Category             | Criteria                                                                                                                                                                                                                                                                                                            |
|----------------------|---------------------------------------------------------------------------------------------------------------------------------------------------------------------------------------------------------------------------------------------------------------------------------------------------------------------|
| Definitely Related   | The event occurs within a plausible time frame after drug administration, aligns with the known reaction profile of the drug, improves upon discontinuation, and recurs upon re-administration.                                                                                                                     |
| Possibly Related     | The event occurs within a plausible time frame after drug administration but does not align with the known reaction profile of the drug. The subject's clinical condition or other treatments may also contribute.                                                                                                  |
| Possibly Unrelated   | The event does not occur within a plausible time frame after drug administration and does not align with the known reaction profile of the drug. The subject's clinical condition or other treatments may contribute.                                                                                               |
| Definitely Unrelated | The event does not occur within a plausible time frame after drug administration and does not align with the known reaction profile of the drug. The subject's clinical condition or other treatments are likely the cause, and the event resolves with disease improvement or discontinuation of other treatments. |
| Unable to Determine  | The event's timing relative to drug administration is unclear, and it resembles the known reaction profile of the drug or could be caused by concomitant medications.                                                                                                                                               |

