#### 8.4.4 Recording and Reporting of Adverse Events

Researchers should meticulously document any adverse events that occur in the subjects, including: a description of the adverse event and all related symptoms, the time of occurrence, severity, end time, measures taken, and the final outcome.

From the time the subject signs the informed consent form until 28 days after the last dose, drug safety assessments are required. All adverse events (both serious and non-serious) should be recorded on the adverse event reporting page of the case report form, using precise medical terminology. Follow-up should continue until the adverse event returns to Grade I or below, or until the investigator deems further follow-up unnecessary (e.g., clinical stability is achieved).

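### The treatment-related adverse event rate is not uniquely defined: Table 2 has no category for an expected, well-timed reaction after a single dose, and the numerator is three categories in one sentence and two in the next

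*Protocol*

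**What the plan says.** Section 2.2.3 names one secondary safety endpoint: "Treatment related adverse events (evaluated using the National Cancer Institute Common Terminology Criteria for Adverse Events (NCI CTCAE) version 5.0"). The synopsis lists the same endpoint first and adds ECG monitoring and blood glucose.

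Section 8.4.3 tells investigators to judge relatedness "using a five-category classification method to evaluate the potential association between adverse events and the study medication". It classes three of the five categories (definitely related, probably related, unable to determine) as adverse drug reactions. The next sentence reads: "When calculating the incidence of adverse events, the sum of these two categories is used as the numerator". The denominator is the number of participants evaluated for safety.

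Table 2 gives the criteria. *Definitely Related* requires plausible timing, agreement with the known profile, and an event that "improves upon discontinuation, and recurs upon re-administration". *Possibly Related* is defined thus: "The event occurs within a plausible time frame after drug administration but does not align with the known reaction profile of the drug". Both unrelated rows require implausible timing and disagreement with the profile. *Unable to Determine* requires unclear timing.

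Section 5.2.1 gives each arm one intravenous dexamethasone dose and one NEPA capsule before chemotherapy. Section 10.2 describes a single observed cycle with allocation open to investigators and participants.

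On the collection period, Section 8.4.4 says that "until 28 days after the last dose, drug safety assessments are required", while the flowchart note says "Safety follow-up will be conducted within 7 days after the last administration".

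**The concern.** A causality table should place the textbook adverse reaction, well timed and already known for the drug, at or near the top of the scale. This table does the reverse: an off-profile event can be called related, and an expected one cannot. Expected dexamethasone reactions matter most here, because Section 1.3.1 gives fewer and milder ones as the reason for lowering the dose.

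Causality is assigned by the investigator when the event is recorded. An analysis plan written later cannot recover a classification for which the criteria had no place. Because the trial is open-label, each off-criteria decision is made with the arm known, so any leaning could differ between arms in the comparison the dose reduction is meant to improve.

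The numerator wording adds a second ambiguity. Two analysts with the same locked data could report different rates and both cite Section 8.4.3.

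**Working it through.** The protocol states no related-event rate, so there is no figure to reproduce. The check is logical, with one illustrative calculation.

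**Step 1. Set out Table 2 as conditions.**

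| Category | Timing | Matches known profile | Further conditions |
|---|---|---|---|
| Definitely Related | plausible | yes | improves on stopping and recurs on re-administration |
| Possibly Related | plausible | no | disease or other treatment may contribute |
| Possibly Unrelated | implausible | no | disease or other treatment may contribute |
| Definitely Unrelated | implausible | no | another cause likely, with resolution in line with it |
| Unable to Determine | unclear | resembles it, or concomitant medication could explain the event | none |

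**Step 2. Apply the design.** With one administration of each drug in one observed cycle (Sections 5.2.1 and 10.2), recurrence on re-administration cannot be observed. *Definitely Related* is therefore out of reach.

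**Step 3. Enumerate timing by profile, with no re-administration.**

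| Timing | On profile | Off profile |
|---|---|---|
| Plausible | **no category** | Possibly Related |
| Implausible | no category | Possibly Unrelated, sometimes also Definitely Unrelated |
| Unclear | Unable to Determine | Unable to Determine only if concomitant medication could explain it |

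The top-left cell is the expected adverse reaction. It matches 0 of 5 categories, whatever the course after dosing and whatever other cause is considered. Read literally, the attainable reaction categories hold only well-timed off-profile events and events of unclear timing.

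**Step 4. Count the numerator.** Section 8.4.3 names three reaction categories and then sums two without saying which. Two of the three can only give an equal or lower rate. If *unable to determine* is the one dropped, an arm's rate falls by the share of its patients whose only reaction events are in that category. The protocol does not give this share. Taking 2% to 15% as an assumption, with 93 per arm from Section 10.1:

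- 93 × 0.02 = 1.9 patients, 2 percentage points
- 93 × 0.15 = 13.9 patients, 15 percentage points

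The between-arm difference moves by the difference between the two arms' shares. The sentence also speaks of adverse event incidence in general; read literally, it would misdefine the all-cause rate too.

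**Step 5. Compare labels.** Section 8.4.3 uses *probably* related and *probably not* related. Table 2 uses *possibly* related and *possibly* unrelated. The SAE form in Appendix 3 also uses *possibly*, and ends with *unrelated* and *unassessable*.

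**Step 6. Compare collection periods (secondary).** Section 8.4.4 runs to 28 days after the last dose. Section 8 runs to the end of the study. The flowchart's adverse event row ends at D7. The safety visit in Section 6.3.2 is at 7 ± 3 days, so day 10 at the latest, and no later contact is scheduled.

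**The case against.** **A rate can still be produced.** Section 8.4.3 asks for an overall assessment, and an experienced investigator will call an expected reaction related whatever the table says. This stands against any inference that the endpoint cannot be computed. It does not make the endpoint well defined: judgement is then replacing the written criteria, with the arm known.

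**The two-category wording is probably a drafting slip.** The preceding sentence names all three categories, and three is the natural reading. That is fair and makes the correction easy, but the text should say it.

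**Re-administration might occur.** Section 1.3.1 describes a second round with double-dose NEPA. The objectives and dosing sections of this protocol cover a single dose, and Section 10.2 a single cycle. Even with re-exposure, an on-profile event that did not recur would still fit no row.

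**Safety does not rest on Table 2 alone.** Glucose is judged on measured values and ECGs are recorded directly. Section 10.6 plans adverse event incidence and severity without a causality filter. This stands: a reader might infer that the whole safety comparison fails, and it does not.

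**The collection periods may be compatible.** A reader might infer that 7 and 28 days contradict each other outright, or that last enrolment and completion both in August 2025 exclude 28 days. The documents support neither. A 7-day visit can sit inside a 28-day reporting period, and the dates are estimated months: a patient dosed on 1 August reaches day 28 on 29 August. What remains is that three end points are stated and nothing is scheduled after about day 10.

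**Conclusion.** The point holds for Table 2 and the numerator wording. An expected, well-timed reaction after the single dose fits none of the five categories, and the related-event numerator is given as both three categories and two. The Table 2 result needs only the text and the single-dose, single-cycle design. The 2 to 15 point shift is illustrative and rests wholly on an assumed share of patients.

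A reader might multiply the dexamethasone side-effect rates in Section 1.3.1 by the arm size to count unclassifiable patients. The documents do not support that: by its cited title, the survey concerned dexamethasone for delayed emesis after moderately emetogenic chemotherapy, whereas this trial gives one dose before chemotherapy.

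The collection period is a reconciliation note, not a second finding. The primary endpoint and sample size are not affected, and the Table 2 gap does not reach the glucose, ECG or all-cause adverse event analyses. The change should be made because a named safety endpoint depends on it and it costs little.

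**What to change.** 1. In Table 2, redefine the middle related category as plausible timing and either consistency with the known profile or no clear explanation by disease or other treatment. Require neither dechallenge nor rechallenge.
2. Use one set of five labels in Section 8.4.3, Table 2 and the SAE form in Appendix 3.
3. Replace the numerator sentence. The drug-related adverse event rate is the number of patients with at least one event classed as definitely related, possibly/probably related or unable to determine, divided by the safety set of Section 11. State separately that all-cause incidence counts every adverse event.
4. Reconcile the adverse event collection period across Section 8, Section 8.4.4, Section 6.3.2 and the flowchart, and apply the same period to both arms.

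The cost is a text amendment and a check of the labels in the electronic case report form. Events already classified under the present table would need re-assessment against the revised criteria, preferably by someone unaware of the arm. No extra patients are needed. Later contacts would be needed only if the reconciled period runs beyond the scheduled visits.
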